### Participants and Procedures

In phase 1, a panel of 8-12 experts, comprising nurses, physicians, and pharmacists, evaluated the relevance and clarity of the proposed items derived from the literature review (content validity). The experts provided written consent to use their sociodemographic and professional characteristics for scientific reporting, as content validity is closely linked to the characteristics of the involved experts. This phase cannot be anonymous to ensure transparency, and variables such as sex, age, academic title, experience in studies testing content validity, and experience in oral anticoagulation were collected.

Once adequate content validity was established (December 2023), data collection commenced at the IRCCS (Istituto di Ricovero e Cura a Carattere Scientifico [Institute for Research and Healthcare]) Policlinico San Donato, using 2 cross-sectional data collection rounds using web surveys. A convenience sampling procedure was used, disseminating the web surveys through social media campaigns, newsletters, and flyers of associations involving anticoagulated patients, such as “Associazione Italiana Cardiopatici Congeniti” (AICCA). Participants for the second round were selected based on the same approach, with communication to prevent overlapping responses from participants who completed the survey.

Quality control measures have been implemented to ensure the integrity and quality of the data collection process: automatic data validation checks are included in the survey software to ensure that all responses are complete and adhere to the required format; unique identifiers were used for each participant to prevent duplicate responses in the dataset; and after data collection, statistical analyses were performed to identify any outliers or inconsistencies in the responses, which were then reviewed for accuracy.

### Sampling Procedure

The sampling procedure will use a cloud-data recording system and web surveys disseminated through social media campaigns, newsletters, and flyers. The local study coordinator and the principal investigator will manage the sampling procedure following good clinical practice principles. An expected response rate of approximately 60% is anticipated, which is considered adequate [20]. This expectation is based on several considerations, including using targeted engagement strategies such as precontacting potential participants and leveraging multiple dissemination channels. In fact, this rate aligns with the upper bound of the confidence interval from a recent meta-analysis, which reported an average response rate of 44.1% across 1071 studies in educational research [20]. Studies achieving similar response rates are those that have successfully implemented strategies to engage participants actively.

### Sample Size

The sample size for phase 1 will be 8-12 experts. The sample size required for phase 2 to perform the Mokken scaling analysis was determined considering the 20 items derived from phase 1 (content validity phase). A simulation-based power analysis was performed in R (R Foundation for Statistical Computing; library “Mokken”), as shown in Multimedia Appendix 1. The aim of the simulation was to estimate a sample size that would provide sufficient statistical power, set at 0.8, to detect a minimum H coefficient of 0.3, indicative of a moderate scale according to Mokken’s hierarchy. The H coefficient in Mokken scaling analysis measures the strength of the hierarchical relationship among items in a scale as it quantifies the extent to which items form a cumulative scale. A custom simulation function was created using R statistical software, with the following parameters defined: 20 items, initial sample (n= 200), number of simulations=100, desired power=80%, minimum H coefficient=0.3, and maximum number of iterations=30. For each simulation iteration, the function generated a matrix of binary data representing responses to the 20 items, with responses simulated under a simple random model (ie, the probability of success was 0.5 for each item). The results from the simulation suggested that a sample size of 500 patients would be needed to achieve the desired power of 0.8 for our MSA. The MSA procedure will help reduce the number of items to the first 10-15 items that define the preparedness for self-monitoring and self-management of oral anticoagulation in adult patients. The required sample size for the second round of data collection will be determined through Monte Carlo simulations, aiming to achieve a power of 0.8 for the confirmatory factor analysis (CFA) model.

### Eligibility Criteria

In phase 1, experts must have at least 1 year of experience in managing patients with VKAs, hold at least a master’s degree in nursing, pharmacy, or an MD degree, and have proficiency in the Italian language. Exclusion criteria for experts include conflicts of interest regarding the topic. In phase 2, patients aged 18 years and older will be included under oral anticoagulation treatment in an anticoagulation clinic for at least 3 months, with appropriate cognitive functioning and the ability to provide informed consent. Patients will be excluded based on more specific criteria to ensure the homogeneity and reliability of our data: those with a high Charlson Comorbidity Index (CCI>4), indicating severe concurrent medical conditions that could confound the study outcomes; patients undergoing any other experimental treatment affecting coagulation; and those with a history of noncompliance with medical regimens as reported by their health care providers.

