**Methods:**

This study comprises 2 main phases, and it adheres to the “COnsensus-based Standards for the selection of health Measurement INstruments” (COSMIN) guidelines for instrument development. The first phase involved the conceptualization of the PERSONAE scale, where a comprehensive literature review and a consensus meeting among experts were conducted to draft the initial items. Face and content validity were then established through an expert panel review. In the second phase (ongoing), a detailed sampling methodology will be used, targeting adult Italian patients on long-term oral anticoagulation. According to a performed simulation-based power analysis, the study aims to recruit a sample size of approximately 500 participants by using a combination of convenience and snowball sampling. Data collection will be facilitated through web-based surveys distributed through social media and patient networks, ensuring a wide and representative sample. Analytical procedures will include Mokken scaling analysis for item selection and confirmatory factor analysis to validate the scale’s structure. In addition, internal consistency will be assessed using Molenaar Sijtsma statistics.

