## Introduction

Vitamin K antagonists (VKAs), such as warfarin, are a group of medicines used to thin the blood, preventing the formation of harmful blood clots that can lead to stroke [1]. They function by inhibiting Vitamin K-dependent coagulation factors, which are essential for blood clotting. This class of medications is particularly vital for reducing the risk of stroke associated with atrial fibrillation and heart valve replacements, especially when direct oral anticoagulants are unsuitable for certain individuals, such as adults with multiple morbidities [1]. The use of oral anticoagulants globally is on the rise, reflecting an increasing need to manage conditions predisposing individuals to increased thromboembolic risks. Currently, about 2 out of every 100 Italians are on oral anticoagulants [2], including both direct and indirect agents [3]. This increasing prevalence underscores the necessity for regular monitoring of prothrombin time and appropriate dose adjustments, as inadequate monitoring and dose management could lead to serious adverse reactions and complications. Several studies have highlighted the risks associated with insufficient monitoring in the last 2 decades [4,5]. For instance, it was highlighted that patients on warfarin who did not have their prothrombin time regularly monitored were at a higher risk of major bleeding complications [4]. A meta-analysis published in 2020 confirmed that with the rising number of patients on oral anticoagulants, there is a proportional increase in adverse events related to inadequate monitoring [5].

People on long-term oral anticoagulation can use point-of-care testing equipment (POCT) to monitor their blood clotting time, typically measured by the international normalized ratio (INR) [6]. In managing their anticoagulant medication, these individuals have 2 primary options: self-management, where they adjust their medication dosage based on a predetermined dose-INR schedule, allowing them greater autonomy and immediate response to INR readings, or self-monitoring, where they measure their INR levels independently but consult health care providers to make dosage adjustments [7]. This distinction is crucial as self-management empowers patients to take full control of their therapy, potentially improving their adherence and outcomes, while self-monitoring still relies on professional guidance for dose adjustments [8,9].

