### Study Procedures for Cross-Sectional Data Collections

Patients who agree to participate will access a web-based survey (SurveyMonkey) through social media channels, mobile messages, or emails. The invitation will include all relevant information about the study’s aim, methods, and tasks required for participation. Patients will confirm the inclusion and exclusion criteria during the initial access, and those who do not meet the criteria can opt out.

The data collection tools will include the PERSONAE scale derived from the content validity phase, a sociodemographic and clinical data form, and a graphic rating scale for assessing patients’ preferences for technology-assisted learning options. Sociodemographic data will include age, sex, marital status, educational level, and occupation, while clinical variables will encompass time in oral anticoagulation, clinical indication for anticoagulation, %TTR, and history of thromboembolic or bleeding complications in the last 3 months. These clinical variables are consistent with previous research, such as the studies that developed measures of knowledge in the same population [21,22], which examined similar sociodemographic and clinical factors to assess anticoagulation knowledge in the Italian population. This alignment ensures that our data collection is grounded in established theoretical frameworks and allows authors to generate hypotheses relevant to our target population.

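### Phase 2 eligibility is not limited to vitamin K antagonist users and the anticoagulant taken is not among the listed variables, although the construct is defined by INR testing and INR-based dosing

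*Protocol article*

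**What the plan says.** For patients, the Eligibility Criteria state that "patients aged 18 years and older will be included under oral anticoagulation treatment in an anticoagulation clinic for at least 3 months". The exclusions concern comorbidity, other experimental treatment affecting coagulation, and noncompliance; none concerns drug class. The abstract describes the phase 2 sampling equally broadly, as "targeting adult Italian patients on long-term oral anticoagulation".

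For the phase 1 panel, the same section does name the class: "experts must have at least 1 year of experience in managing patients with VKAs".

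The Introduction opens with VKAs as the therapy of interest, mentions direct agents as the alternative, and reports that "about 2 out of every 100 Italians are on oral anticoagulants [2], including both direct and indirect agents [3". It then defines the two behaviours that the scale addresses. In self-management, "they adjust their medication dosage based on a predetermined dose-INR schedule"; in self-monitoring, "they measure their INR levels independently but consult health care providers to make dosage adjustments".

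The section on study procedures lists what is collected: "clinical variables will encompass time in oral anticoagulation, clinical indication for anticoagulation, %TTR, and history of thromboembolic or bleeding complications in the last 3 months". The anticoagulant itself is not in that list.

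**The concern.** The construct is preparedness to test one's own INR and to act on the result. If the sample also holds people whose treatment is not steered by INR, their answers to testing and dosing items may reflect their drug class and not their level of preparedness.

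The analyses exposed are the ones that build the scale. Mokken scaling reduces the 20 items to 10-15 using scalability (weak scale from H of 0.3), monotonicity and invariant item ordering, and a one-factor CFA follows in a second sample. An unrecorded class effect could cause core self-testing items to be dropped, or could create item covariance that looks like scalability. The Data Analysis section names the Charlson index and unspecified other confounders for possible invariance testing. Class can be one of those only if it was recorded.

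**Working it through.** The article states no figure on this point, so there is none to reproduce. The check is mainly textual.

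**Step 1: population against construct.**

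| Element | Drug class in the article |
|---|---|
| Background and rationale (Abstract, Introduction) | VKA |
| Definitions of self-monitoring and self-management (Introduction) | INR testing; dosing by INR |
| Expert criterion (Eligibility Criteria) | VKA, named |
| Use of the term oral anticoagulants (Introduction) | Direct and indirect agents |
| Patient criterion (Eligibility Criteria) | Oral anticoagulation, class not named |
| Sampling target (Abstract) | Oral anticoagulation, class not named |

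The first three rows point to VKA therapy; the last three do not confine the sample to it.

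**Step 2: can class be recovered from the listed data?** Four clinical variables are listed: time on treatment, indication, %TTR and complications. Indication does not identify the drug. A blank %TTR does not either, since a VKA user may not know the value. The surveys are anonymous (Ethical Considerations) and respondents confirm eligibility themselves, so the plan provides neither a clinician check nor a way to ask later.

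**Step 3: which way could a mixed sample move H?** This is an illustration under assumptions, not an estimate for this trial. Loevinger's H is the sum over item pairs of the observed covariances, divided by the sum of the largest covariances possible given the item marginals. Item H uses only the pairs that contain the item.

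Assumptions: 20 five-point items, n = 500, 60 replicates per scenario; latent response = λθ + √(1−λ²)ε − item location, with λ = 0.6 or 0.7; 8 of the 20 items INR-specific; non-VKA share f = 0, 0.25 or 0.5. Non-VKA users answer the INR items either unrelated to the trait, or low (latent response lowered by 2 units). The number of INR-specific items, the loadings and f are all assumed, because the documents do not give them.

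Mean H for f = 0 / 0.25 / 0.5:

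| λ | Non-VKA answers to INR items | Scale H | INR items | Other items |
|---|---|---|---|---|
| 0.6 | unrelated | 0.36 / 0.30 / 0.24 | 0.36 / 0.27 / 0.18 | 0.36 / 0.32 / 0.29 |
| 0.7 | unrelated | 0.49 / 0.41 / 0.32 | 0.49 / 0.36 / 0.24 | 0.49 / 0.43 / 0.38 |
| 0.6 | low | 0.36 / 0.36 / 0.36 | 0.36 / 0.41 / 0.42 | 0.36 / 0.32 / 0.30 |
| 0.7 | low | 0.49 / 0.46 / 0.46 | 0.49 / 0.49 / 0.50 | 0.49 / 0.43 / 0.42 |

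With unrelated answers, the INR items fall below 0.3 at f = 0.5 for both loadings, and already at f = 0.25 for λ = 0.6. With low answers, scale H hardly moves, the INR items hold or gain, and the other items lose. The direction therefore depends on how non-VKA users respond. Invariant item ordering and CFA fit were not simulated.

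**Step 4: %TTR.** Regression imputation starts at 5% missing, which is 0.05 × 500 = 25 respondents. If that many leave %TTR blank because no INR is monitored, the rule would impute a quantity that does not exist for them.

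**The case against.** The strongest reply is that the article uses oral anticoagulation loosely for INR-managed treatment. It says that people on long-term oral anticoagulation can self-test their INR, it describes the experience of the VKA-qualified experts as experience in oral anticoagulation, and its remark on direct agents is epidemiological. It never says in words that INR and %TTR apply only to VKAs. This shows that the authors may well have intended VKA users. It does not make the criterion say so, and respondents screen themselves against the criterion as worded.

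A reader might infer several stronger things that the documents do not support:

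- *That any oral anticoagulant user qualifies.* The criterion also requires at least 3 months in an anticoagulation clinic, which may enrich for VKA users. How far is not stated.
- *That class certainly cannot be recovered.* The full data form and the eligibility screen are not shown and could hold a drug field. What stands is that the article's explicit list has none.
- *That the scale will be distorted.* The item wording is not shown. The items also cover adherence, lifestyle and technology, and the stem asks how prepared patients feel, not what they do. The article itself reports barriers to self-testing in Italy, so VKA users may not perform these tasks either.
- *That a given number of the 500 are affected.* The documents give no share, and an assumed one multiplied by 500 says nothing about this trial.
- *That imputing %TTR corrupts the main results.* %TTR does not enter the Mokken analysis or the reliability coefficient. It could enter the CFA only as a conditional covariate.

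**Conclusion.** The point holds as a mismatch between the eligible population and the construct, with no listed variable by which to detect or correct it. The conclusion rests on the article's wording and on its list of clinical variables being complete as to the drug taken.

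The consequence is a risk of unknown size and direction for item selection and for the one-factor model. The illustration shows only that moderate shares of non-VKA users can move item H across the 0.3 threshold under some response patterns and leave scale H almost unchanged under others. The %TTR issue is secondary and concerns description and possible covariates.

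**What to change.** - Align the patient criterion with the VKA-based construct, or state explicitly that both classes are intended and why.
- Add one required survey question on the anticoagulant taken, from round 2 onward. If the round 1 form already holds it, use it.
- Make VKA users the primary set for the Mokken analysis and the CFA. If both classes are kept, test item bias by class.
- Code %TTR as not applicable, not as missing, where no INR is monitored, and keep those respondents out of the imputation rule for that variable.
- If round 1 did not record class, report this as a limitation of the item selection and check the selected items in the VKA subset of round 2.

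The cost is one extra question and somewhat slower round 2 recruitment. Round 1 ran from January to May 2024 with anonymous responses, so a new question cannot repair those data.

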### Study Procedures for Cross-Sectional Data Collections

Patients who agree to participate will access a web-based survey (SurveyMonkey) through social media channels, mobile messages, or emails. The invitation will include all relevant information about the study’s aim, methods, and tasks required for participation. Patients will confirm the inclusion and exclusion criteria during the initial access, and those who do not meet the criteria can opt out.

The data collection tools will include the PERSONAE scale derived from the content validity phase, a sociodemographic and clinical data form, and a graphic rating scale for assessing patients’ preferences for technology-assisted learning options. Sociodemographic data will include age, sex, marital status, educational level, and occupation, while clinical variables will encompass time in oral anticoagulation, clinical indication for anticoagulation, %TTR, and history of thromboembolic or bleeding complications in the last 3 months. These clinical variables are consistent with previous research, such as the studies that developed measures of knowledge in the same population [21,22], which examined similar sociodemographic and clinical factors to assess anticoagulation knowledge in the Italian population. This alignment ensures that our data collection is grounded in established theoretical frameworks and allows authors to generate hypotheses relevant to our target population.

### Data Analysis

The data analysis will involve the use of various statistical methods to develop and validate the PERSONAE scale.

For the first data collection round, MSA will be conducted using the “mokken” package in R [23]. MSA allows for the hierarchical evaluation of items, and the most relevant items that measure preparedness for self-monitoring and self-management of oral anticoagulation will be selected for the PERSONAE scale [24]. Loevinger’s coefficient of homogeneity function will be used to assess the scalability of the items. Monotonicity violations will be checked, and violations below 80 will be consistent with the requirements of a Mokken scale [23,25]. Loevinger’s coefficients of homogeneity (H) at the scale, item, and pairs of items level will be computed, where H values equal to or greater than 0.3, 0.4, or 0.5 indicate weak, moderate, or strong scales, respectively [23,25]. Item pairs violating monotonicity will be excluded, and floor and ceiling effects in data distribution will be assessed. Invariant item ordering (IIO) will be performed to further narrow down the pool of questions based on monotone homogeneity [25]. The IIO procedure will remove items one at a time until no significant violations are found. The Htrans (H^T^) coefficient will express the accuracy of the IIO selection, and H^T^>0.3 will denote proper IIO process and consistent Mokken scales. The final set of questions will be used to calculate ρ coefficients for reliability using the Molenaar-Sijtsma technique [26]. This approach is particularly adequate for assessing reliability in MSA because it provides a robust estimate of the internal consistency for nonparametric scales. The Molenaar-Sijtsma technique is well-suited for evaluating the scalability and reliability of the items within the scale, ensuring that the PERSONAE scale reliably measures the construct of preparedness for self-monitoring and self-management of oral anticoagulation.

CFA will be used to cross-validate the plausible unidimensional structure of the PERSONAE scale derived from the MSA, theoretically containing 10-15 items, using Mplus 8.1 (Muthén and Muthén, 2017). An unrestricted and unspecified model will be used with a maximum likelihood robust estimation of parameters. A confirmatory factor analysis with covariates will be used to estimate measurement invariance between subgroups if linear relationships between participant characteristics and the scale’s total score are detected [27]. Modification indices will be explored to identify items causing a violation of invariance. Items causing invariance will be evaluated for possible deletion from the final scale. The adequacy of confirmatory factor analyses in explaining sample statistics will be assessed using various fit indices, such as chi-square, chi-square/degree of freedom, comparative fit index, Tucker-Lewis index, and root mean square error of approximation [28]. Invariance testing based on different levels of CCI and other potential confounders will be considered if needed and is feasible to ensure that the scale functions equivalently across groups with varying levels of comorbidity and demographics.

Missing data will be managed using an available-case approach for missingness lower than 5% or regression imputations for missingness equal to or higher than 5%, assuming missing at random. The significance level for all analyses will be set at 5%. The software used for the analysis will include Mplus (version 8.1, Muthén and Muthén), IBM SPSS Statistics for Microsoft Windows version 27, and R (version 4.2.1, R Foundation for Statistical Computing).

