**Results:**

The scale’s content derived from phase 1 (process completed in December 2023) is grounded in a comprehensive literature review and based on the assessments of a panel of 12 health care expert professionals. The PERSONAE scale derived from phase 1 encompasses 20 items reflecting essential behaviors needed to assess the preparedness for self-monitoring and self-management of oral anticoagulation. Each item obtained a content validity ratio higher than 0.67, which is the critical content validity ratio indicating the minimum level of agreement among the experts for an item to be considered essential beyond the level of chance at a significance level of .05 for a 1-tailed test. From January 2024 to May 2024, we conducted the initial round of data collection and use Mokken scaling analysis to select items. A second round of data collection for confirmatory factor analysis was scheduled from June 2024 to September 2024, which will validate the scale’s unidimensional structure. We expect to achieve robust psychometric properties, including high internal consistency and validated constructs.

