While self-monitoring and self-management approaches have garnered strong evidence for their effectiveness and cost-effectiveness, a Cochrane review highlighted the need for further research into factors influencing individuals’ preparedness for self-testing [8]. These factors include both psychological preparedness and preparedness in terms of objective equipment. Psychological preparedness encompasses patients’ self-management knowledge, motivations for medical attention, health literacy, self-efficacy, and perceived and actual support systems [13,16]. Specifically, patients’ knowledge about self-management affects their ability to understand and manage their treatment, while motivations for seeking medical attention could influence their commitment to regular monitoring. Health literacy impacts their ability to comprehend medical instructions and make informed decisions, and self-efficacy relates to their confidence in performing self-testing tasks [17]. Finally, perceived and actual support systems are crucial in providing the necessary resources and emotional support for effective self-management. Preparedness in terms of objective equipment involves access to and familiarity with POCT devices and other necessary tools. Evaluating preparedness for self-management and self-monitoring is therefore crucial in tailoring health care delivery, enhancing efficiency, and adequately preparing patients for self-testing [18]. The interaction between psychological preparedness and preparedness regarding objective equipment is critical. Patients who are psychologically ready but lack the necessary equipment, or vice versa, may not effectively self-manage their condition. Therefore, both aspects must be addressed to ensure successful self-management and self-monitoring.

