## Methods

### Study Design

This methodological, multiphase study comprises 2 main phases to develop and validate the PERSONAE scale for assessing the preparedness for self-monitoring and self-management of oral anticoagulation in adult patients. The protocol adheres to the “COnsensus-based Standards for the selection of health Measurement INstruments” (COSMIN) guidelines for instrument development [19].

Phase 1 focused on conceptualizing the PERSONAE scale through a developmental methodological approach involving 3 primary steps. First, a literature review was conducted to identify all relevant elements related to the preparedness for self-monitoring and self-management of oral anticoagulation (anticipated between May 2023 and July 2023). This review was recently published elsewhere [13]. Second, a consensus meeting among developers was held to examine the findings of the literature review and endorse its synthesis (anticipated time: September 2023). Finally, the situations representing patients’ preparedness will be operationalized, and an external panel of experts, including nurses, physicians, and pharmacists, will determine the face and content validity of the newly developed scale (anticipated time: October 2023). Phase 2 focused on the validation procedures. Initially, the PERSONAE scale, containing items with acceptable content validity, was used for cross-sectional data collection from January to May 2024. The Mokken scaling analysis (MSA) procedure will be used to assess how the items in the first version of the scale behave in response to varying levels of the theoretical latent trait (preparedness). MSA is preferred over exploratory factor analysis in this study as it allows selecting items with the highest scalability, leading to a brief, unidimensional measure computed in a single score. Once a stable unidimensional PERSONAE scale is developed, a second round of cross-sectional data collection was performed from June to September 2024 to cross-validate the plausible unidimensional structure of the scale.

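### Round 2 judges the one-factor structure by global fit alone and names no rival model, so a small but distinct set of equipment items could pass unnoticed

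*Protocol article*

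**What the plan says.** The Data Analysis section gives the confirmatory factor analysis (CFA) one task: "CFA will be used to cross-validate the plausible unidimensional structure of the PERSONAE scale derived from the MSA". The Abstract's Results paragraph presents the outcome as settled, saying of the second round "which will validate the scale’s unidimensional structure". Study Design commits to the single score, describing the Mokken selection as "leading to a brief, unidimensional measure computed in a single score".

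On how the structure will be judged, Data Analysis says "The adequacy of confirmatory factor analyses in explaining sample statistics will be assessed using various fit indices". It then lists chi-square, chi-square/df, CFI, TLI and RMSEA as examples, without cut-offs. Modification indices have a different purpose: "Modification indices will be explored to identify items causing a violation of invariance". No two-factor or other competing model is named.

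The Introduction describes what bears on preparedness as having two sides: "These factors include both psychological preparedness and preparedness in terms of objective equipment". It adds that the two can come apart: "Patients who are psychologically ready but lack the necessary equipment, or vice versa, may not effectively self-manage their condition".

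**The concern.** Global fit asks whether one factor reproduces the whole correlation matrix tolerably well. It does not ask whether a particular subset of items measures something else. If that subset is small, its misfit is averaged over many item pairs that fit well, and RMSEA and CFI can look good although the factors are distinct. The protocol's own background supplies the obvious alternative, psychological against equipment preparedness, but the printed plan does not compare it with one factor.

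At stake is the main conclusion of round 2. The Discussion foresees the total score helping to identify patients suited to self-testing and to adjusting their own medication. If the two aspects are separate, one total can hide the mismatch that the Introduction warns about.

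**Working it through.** **Inputs from the article.** 10-15 items enter the CFA, responses are on a 5-point scale, estimation is robust maximum likelihood, and alpha is 0.05. The round 2 sample size is not given; it is left to Monte Carlo simulation. The only computed sample size, 500, belongs to the Mokken analysis, so there is no plan figure to reproduce here.

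**Assumptions, none given in the article.** Main example: p = 12 items, all loadings λ = 0.7, q equipment items, factor correlation φ, n = 300. Cut-offs in common use: RMSEA ≤ 0.06 with CFI ≥ 0.95 (strict), or RMSEA ≤ 0.08 with CFI ≥ 0.90 (loose). Items are treated as continuous. The CFA is taken to be a one-factor model, although the text reads "An unrestricted and unspecified model will be used with a maximum likelihood robust estimation of parameters".

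**Step 1: fit of one factor when two are true.** Build the population correlation matrix Σ from two correlated factors and fit one factor by ML, giving the minimum discrepancy F. With 12 items, df = 78 − 24 = 54. Then RMSEA = √(F/df) and CFI = 1 − F/F0, where F0 = −ln|Σ|.

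- q = 2, φ = 0.6: F = 0.1517, F0 = 4.888. RMSEA = √(0.1517/54) = 0.053; CFI = 1 − 0.1517/4.888 = 0.969.
- q = 2, φ = 0.7: F = 0.1089, F0 = 4.992. RMSEA 0.045; CFI 0.978.
- q = 3, φ = 0.8: F = 0.1513, F0 = 5.012. RMSEA 0.053; CFI 0.970.

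All three meet the strict cut-offs.

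**Step 2: would these items survive round 1?** Approximate an equipment item's H by its mean correlation with the other items: H ≈ [(p − q)λ²φ + (q − 1)λ²]/(p − 1).

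- q = 2, φ = 0.6: (10 × 0.49 × 0.6 + 0.49)/11 = 0.31.
- q = 2, φ = 0.7: (10 × 0.49 × 0.7 + 0.49)/11 = 0.36.
- q = 3, φ = 0.8: (9 × 0.49 × 0.8 + 2 × 0.49)/11 = 0.41.

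All are at or above 0.3, the article's floor for a weak scale.

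**Step 3: power at n = 300.** The two-factor model is true, so both tests have noncentrality (n − 1)F: 299 × 0.1517 = 45.4, 32.6 and 45.2 for the three cases. The 1-df comparison (critical value 3.84) has power of about 1.00 in each. The global chi-square on 54 df has power 0.956, 0.824 and 0.955.

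**Step 4: where global fit is already enough.** With q = 4, λ = 0.7 and φ = 0.5, one factor gives RMSEA 0.118 and CFI 0.834, a clear failure.

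**Step 5: how wide the gap is.** The grid has 180 settings (10, 12 or 15 items; 2-5 equipment items; loadings 0.6, 0.7 or 0.8; five factor correlations; 36 settings per correlation). Settings in which one factor passes and the approximate item H is at least 0.3:

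| φ | strict cut-offs | loose cut-offs |
|---|---|---|
| 0.3 | 0/36 | 0/36 |
| 0.5 | 0/36 | 1/36 |
| 0.7 | 5/36 | 9/36 |
| 0.8 | 16/36 | 23/36 |
| 0.9 | 30/36 | 36/36 |

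**The case against.** **Round 1 screens items first.** The Mokken step selects for scalability, and the CFA sees only the survivors. This largely stands. With 2 equipment items at correlation 0.5, the approximate item H is only 0.20 (loading 0.6) to 0.27 (loading 0.7), so those items would probably be dropped, even though one factor would fit well if they stayed (RMSEA 0.041-0.059, CFI 0.961-0.968). The screen is not complete, however. The article uses 0.3 to label scales, while its explicit removal rules concern monotonicity and invariant item ordering. The cases in Steps 1 and 2 clear 0.3 in any event.

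**The two-factor structure is inferred.** The Introduction describes aspects of preparedness, not subscales. Elsewhere the items are derived from self-care behaviours, and the content is described as knowledge, self-efficacy and practical application. The item list is in an appendix that is not shown. This stands: the number of equipment items is an assumption, and the fix must depend on it.

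**A condensed article may leave rival models and cut-offs to a fuller document.** The list of indices is open-ended. So it can be said only that the article names no rival model, not that none will be fitted. Missing cut-offs are not the point here. The article does commit itself on purpose, software, estimator and type of criterion, and then announces the conclusion.

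**Chi-square is among the criteria and often rejects too.** True (Step 3), but no rule says what a significant chi-square leads to when RMSEA and CFI look good. Nor does a global rejection show which items are responsible.

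A reader might infer that round 2 would confirm one dimension whether or not it is true. The document does not support that: the named indices can reject one factor, and do so in most settings where the factors are clearly separate.

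**Conclusion.** The concern holds in a limited form. As printed, round 2 rests the claim of one dimension on global fit of one model and sets no rival beside it, although the Introduction describes two aspects that can diverge. A small equipment factor that survives round 1 can then go unseen, chiefly with 2 items correlating 0.6-0.7 with the main factor, or 3 items at about 0.8. There RMSEA is about 0.045-0.053 and CFI about 0.97-0.98, while the direct comparison has power of about 1.00 at n = 300.

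Loadings, item split, factor correlation, sample size and cut-offs are all assumed. At correlations of 0.8-0.9, where misses are most common, a single score also does less harm. This is a worthwhile sharpening of the test; using a one-factor CFA on a fresh sample is not itself an error.

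**What to change.** Make the addition conditional: if two or more equipment items remain after round 1,

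1. assign each retained item to the psychological or the equipment factor, and record the assignment before the round 2 data are analysed;
2. fit a correlated two-factor model beside the one-factor model;
3. compare them with the scaled chi-square difference test that robust ML requires;
4. report the factor correlation with its 95% CI;
5. base the claim of unidimensionality on this comparison together with global fit, and report the two-factor structure if the factors are clearly distinct.

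The difference test should not decide alone. With 4 equipment items, loading 0.7 and correlation 0.9, its power is already 0.98 at n = 200, so it will flag factors that are nearly the same. A fixed rule that the lower confidence limit must exceed 0.85 is not advised either. With 2 equipment items and n = 300, a true correlation of 0.95 would meet it only 41% (loading 0.6) to 81% (loading 0.7) of the time.

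The cost is one more model on the same data in the same software and a few sentences of plan text. The downside is that the claim of unidimensionality may fail where global fit alone would have passed it.
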